### Adherence strategies

The BEeT platform contains in-built reminders to prompt engagement with the intervention. These include email notifications to alert participants to when a new online BEeT session is available and an automatic text message at approximately 6 p.m. to participants who have not made a food monitoring entry in the previous 24-h period. In addition, participants will be able to create their own personalised reminders specific to their weekly goals.

Additional efforts to re-engage participants in the pure self-help BEeT or WLC groups will consist of written contact via email to the participant after one week of disengagement, a phone call from researchers or clinicians after two weeks consecutive weeks of disengagement, and a letter to the participant and GP after three consecutive weeks of disengagement. The participant will be given an additional two weeks to reengage before they are discontinued from the trial.

### Contaminant care

Participants will be permitted to seek regular consultation with other health professionals (e.g., dietitian, psychiatrist) whilst actively engaged in the trial, regardless of arm. Concurrent psychological treatment will only be permitted if it is addressing co-occurring mental health difficulties (e.g., anxiety and low mood) and not the eating disorder. Anyone receiving psychological treatment for their ED will be ineligible for the trial.

## Outcomes

Data will be collected via online self-report assessments. Table 2 provides an overview of assessment points and outcome measures.

**Table 2 Tab3:** Schedule of enrolment, interventions, and assessments according to SPIRIT

	TIMEPOINT**	STUDY PERIOD						
		Enrolment	Allocation	Post-allocation				
		− T_1_	0	T_0_	Weekly monitoring	T_1_	T_2_	T_3_
**Enrolment**	Eligibility screen	X						
	GP Clearance	X						
	Informed consent	X						
	Allocation		X					
**Interventions**	Clinician-supported BEeT							
	Pure self-help BEeT							
	WLC							
**Assessments**	Demographics			X				
	General mental health			X				
	Self-harm and suicidality risk assessment			X	X	X	X	X
	Eating disorder examination questionnaire (EDE-Q)			X		X	X	X
	Eating disorder examination questionnaire-short (EDE-QS)				X			
	Kessler psychological distress scale (K10)			X	X	X	X	X
	Eating disorder quality of life questionnaire (EDQOL)			X		X	X	X
	Three-factor eating questionnaire (TFEQ)			X		X	X	X
	Young schema questionnaire			X		X	X	X
	Body mass index (BMI)			X	X^1^	X	X	X
	European quality of life-5 dimensions-5 levels (ED-5D-5L)			X		X	X	X
	Evaluation of external health services utilised			X		X	X	X
	Implementation surveys					X		
	Working alliance inventory-short revised (WAI-SR)^2^					X		
	Working alliance inventory for online interventions-short form (WAI-TECH-SF)					X		

**T_0_ = baseline assessment, T_1_ = 12 week assessment (post-intervention), T_3_ = 24 week assessment (3 month follow up), T_3_ = 36 week assessment (for WLC only)

^1^BMI measured in fourth week of participation. Also measured weekly from fifth to tenth week for participants where rapid weight loss is indicated

^2^Only administered to clinician-supported BEeT participants

### Primary outcome

The primary outcome is frequency of objective binge episodes as measured by the eating disorder examination questionnaire (EDE-Q) [53]. EDE-Q is a 30-item self-report questionnaire used to assess frequencies of core ED behaviours, including binge episodes and compensatory behaviours, and attitudinal aspects of ED psychopathology across the preceding 28 days. The EDE-Q upholds good reliability (Cronbach’s α = 0.90) [54].

### Secondary outcome measures

#### Measures of eating disorder psychopathology:

*EDE-QS* A shorter 12-item version derived from the EDE-Q, the eating disorder examination questionnaire-short (EDE-QS) assesses ED behaviours and psychopathology severity in the preceding seven days [55]. The EDE-QS is psychometrically and conceptually sound and has good reliability (Cronbach’s α = 0.90) [55, 56].

*EDQOL* The eating disorder quality of life questionnaire (EDQOL) is a disease-specific measure of health-related quality of life [57]. The EDQOL contains 25-items which assess impairment of the ED upon four primary domains: psychological, physical/cognitive, financial, and work/school. The EDQOL has good reliability (Cronbach’s α = 0.90) [57].

*TFEQ* The three factor eating questionnaire (TFEQ) is a 51-item self-report assessment which measures three dimensions of eating behaviour: cognitive restraint of eating, disinhibition/loss of control, and hunger [58]. The TFEQ has been shown to have good reliability across all three dimensions [58].

#### Measures of general mental health psychopathology

*K10* The Kessler Psychological Distress (K10) is a 10-item self-report questionnaire used to monitor the degree of psychological distress [59]. There is evidence to support the reliability of the K10 as a measure of negative emotionality [60, 61, 62].

*YSQ-S3* The young schema questionnaire-short form (YSQ-SF) is a self-report questionnaire which assesses early maladaptive schemas thought to contribute to underlying dysfunctional beliefs and associated psychopathology [63].

*EQ-5D-5L* The five-dimensional European Quality of Life instrument (EQ-5D-5L) will be used to measure the impact of illness upon participants’ mobility, self-care, usual activities, pain/discomfort, and anxiety/depression as well as an overall health score [64]. Utility weights will be obtained and used, along with life years, to calculate Quality Adjusted Life Years (QALYs).

### Other measures regarding the intervention

*WAI-SR* The working alliance inventory-short revised (WAI-SR) is a 12-item self-report assessment which examines the degree of therapeutic alliance experienced by the patient with the clinician across three subscales: bond, task, and goal [65]. It is a widely used measure with good psychometric properties [66].

*WAI-TECH-SF* Working alliance inventory for online interventions-short form (WAI-TECH-SF) is adapted from the WAI-SR and aims to assess the degree of therapeutic alliance between the patient and internet-based self-help programs [67]. It is also a self-report measure with 12-items and has been shown to be a reliable questionnaire [67].

#### Demographics

Demographic characteristics will be collected using a self-designed questionnaire. These include age, gender, occupation, marital status, level of education, income, cultural background/ethnicity, and setting of residence.

#### General mental health

A self-designed questionnaire will collect information regarding the participant’s perception of their current primary and secondary mental health concern (e.g., eating/weight issues, anxiety, depression etc.), history of mental health difficulties, and treatment status (e.g., type of mental health service and treatment being accessed).

#### Self-harm and suicidality risk assessment

Participants’ history of suicidal and self-harming thoughts or behaviours will be assessed using a self-designed questionnaire. It measures severity of suicidality (e.g., suicidal thoughts, suicide attempts etc.) and deliberate self-harm (e.g., urges to self-harm, self-harm actions) in the previous 12 months to 28 days (pre-post treatment and follow up assessments) and previous seven days (weekly assessments).

#### Participant evaluation of external health services utilised

This purpose-built survey will capture information regarding the healthcare resources used (to calculate costs) of participants. Participants will be asked to report the number of health practitioners they have visited in the previous 28-days, including the type/speciality (e.g., GP, psychiatrist, dietitian, physiotherapist etc.), the number of visits/appointments, and the cost per visit.

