### Trial design and setting

This study is a multisite, three-arm randomized controlled trial inclusive of two active interventions and a WLC. Participants will be recruited from the general community in Australia via advertisements on health websites and social media, referrals made from health professionals, and paper advertisements in mental health and medical clinics. If considered eligible following a screening call, the participant will be instructed to complete a standardised medical assessment with their general practitioner (GP) prior to entry to the study. After providing written informed consent, participants will be randomised to either the WLC condition or one of the intervention conditions, including pure self-help BEeT or clinician-supported BEeT. The intervention is entirely via digital modalities, including (1) *online eTherapy platform* and (2) *secure videoconferencing platform* (only for participants receiving clinician-supported BEeT). Participants randomised to the clinician-supported BEeT condition will engage in telemedicine sessions delivered by clinicians based at one of the following sites: specialist eating disorder outpatient clinic, adult community mental health team, university-based research team, and youth mental health clinic (headspace). All sites are based within New South Wales, Australia. See “Appendix A” for a list of study sites. Participants will be assessed at baseline (T0), weekly, post-intervention (T1: 12 weeks), and at 3-month follow-up (T2). The study commenced in May 2020. The study protocol has been approved by a Human Research Ethics Review Board (HREC #X18-0486). See Fig. 1 for an overview of the study process.

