A within-trial economic evaluation will be conducted to determine the cost-effectiveness of clinician-supported BEeT compared to pure self-help BEeT and then to the WLC from a health system perspective using individual-level data. It is crucial that the cost-effectiveness study runs alongside the clinical trial to ensure the health economic evidence is directly related to the outcomes (patient experience, clinical outcomes and quality of life) and costs of study participants (who represent an eligible population in the real world) and can immediately be used by decision-makers in the translation of results into policy and practice (including scaling-up). A cost-utility framework which expresses the main outcomes as Quality Adjusted Life Years (QALYs) will be adopted. The main hypothesis is that the Incremental Cost Effectiveness Ratios (ICERs) are favourable of clinician-supported BEeT at 12 weeks i.e. ICER < $50,000 per QALY gained. We will also assess whether the effect of clinician-supported BEeT is sustained at 3 months and re-calculate the ICERs. A utility-based and disease-generic quality of life measure, EQ-5D-5L, and a disease-specific measure, EDQOL, will be considered in the health economics analysis. Using a health system perspective, we will also be adopted to measure resource use (costs) and other benefits related to the participants and healthcare providers, including implementation costs such as clinician time costs to complete the training course and to deliver the programs. A cost questionnaire (database) will be developed specifically for this clinical trial. This questionnaire will be used to measure the type, amount and value of resources used (and hence adopting a “bottom up” costing approach). A secondary analysis will consider participants’ need for additional technologies or equipment (e.g. laptop, tablet) and time costs for completing treatment sessions. Results will be presented as ICERs which will be calculated as the difference in total costs between clinician-supported compared to pure self-help BEeT (and then compared to WLC) divided by difference in QALYS. Sensitivity analysis will be undertaken.

For the main trial analysis, data will be analysed using IBM SPSS (Version 22.0.0.0, Chicago, IL).

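### The economic analysis plans no ICER for pure self-help BEeT against waitlist, although Aim 3 includes that comparison, and its only scheduled service-use survey observes 28 of the 84 days behind the 12-week ICER

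*Protocol article*

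**What the plan says.** Study objectives gives, as the third aim, an economic comparison of the waitlist control (WLC) with each of the two BEeT programmes.

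The economic part of Statistical methods lists its contrasts twice, and both times there are two: supported against self-help, then supported against WLC. The second listing defines the ICER as the difference in total costs for "clinician-supported compared to pure self-help BEeT (and then compared to WLC) divided by difference in QALYS". The main economic hypothesis is that the ICERs are "favourable of clinician-supported BEeT at 12 weeks i.e. ICER < $50,000 per QALY gained". They are to be recalculated at 3 months, and a sensitivity analysis is promised without detail.

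On the cost side, the section on external health services says: "This purpose-built survey will capture information regarding the healthcare resources used (to calculate costs) of participants". The look-back is fixed: "Participants will be asked to report the number of health practitioners they have visited in the previous 28-days". In Table 2 the row "Evaluation of external health services utilised" is marked at T0, T1, T2 and T3 and is blank under weekly monitoring. T1 is at 12 weeks, the 3-month follow-up is at 24 weeks, and the 36-week assessment is for WLC only. Programme costs are counted separately, "including implementation costs such as clinician time costs to complete the training course and to deliver the programs". Statistical methods adds: "A cost questionnaire (database) will be developed specifically for this clinical trial". It gives no recall period or schedule for that instrument, and Table 2 lists no other resource-use survey.

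**The concern.** There are two substantive problems and one of wording.

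First, the stated analysis answers only half of a stated aim. The Discussion presents pure self-help as an option that services could adopt in its own right. Its value against no treatment is therefore a decision the trial should inform, most of all if clinician support turns out not to be worth its extra cost.

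Second, an ICER at 12 weeks needs costs for 12 weeks. External service use is observed in only the last third of that period, and the article does not say how the first two thirds are to be costed. The observed third is also not typical of the rest.

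Third, a ratio criterion changes meaning with the sign of its denominator, and the plan writes the criterion as a ratio.

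**Working it through.** **Contrasts, side by side**

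| Contrast | Aim 3 | Statistical methods |
|---|---|---|
| Supported vs WLC | yes | yes |
| Pure self-help vs WLC | yes | no |
| Supported vs pure self-help | no | yes |

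Aim 3 and the analysis share one contrast. The point estimates for the missing one can be recovered. With C for mean cost, S supported, H self-help and W waitlist, (C_S − C_W) − (C_S − C_H) = C_H − C_W, and the same holds for QALYs. The uncertainty cannot be recovered in this way, because the two planned differences share arm S and are correlated.

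**Days observed**

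- Inputs: recall of 28 days (external health services section); T1 at 12 weeks = 84 days and follow-up at 24 weeks = 168 days (Trial design and setting; Table 2).
- The T0 survey looks back before baseline and adds no post-baseline days.
- To week 12: 28/84 = 33.3%. The window starts at 84 − 28 = 56 days, so it is weeks 9-12, and weeks 1-8 are unobserved.
- To week 24: (28 + 28)/168 = 56/168 = 33.3%.

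**Whether weeks 9-12 can stand for weeks 1-8**

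Multiplying the T1 figure by 84/28 = 3 is exact only if the rate of service use is constant over the 12 weeks. Three features of the protocol speak against assuming that.

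- BEeT is a 10-week programme (70 days). Nominally, 84 − 70 = 14 of the 28 observed days fall after it ends.
- WLC participants are offered BEeT after ten weeks, so the same 14 days fall after that offer.
- Under Risk management, weight is checked at week four and the GP is alerted to rapid weight loss. Any GP visits that this prompts in weeks 5-8 are not seen.

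The article also contradicts itself on timing. The Waitlist control section ties T1 to ten weeks, while Trial design and setting and Table 2 put it at 12. If WLC were surveyed at week 10, their window would start at 70 − 28 = 42 days (weeks 7-10) and would not match that of the other arms.

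**Size of bias**

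The documents give no expected costs, utilities or variances for the economic analysis, so neither the size nor the direction of a bias in the ICER can be computed.

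**The criterion**

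This is an algebraic illustration with assumed values. A cost difference of +$500 with a QALY difference of −0.005 gives an ICER of −$100,000. So does −$500 with +0.005. Net monetary benefit, 50,000 × ΔQALY − ΔCost, separates them: −250 − 500 = −$750 against +250 + 500 = +$750.

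**The case against.** **On the recall window.** A reader might infer that four weeks of cost are to be divided by twelve weeks of QALYs. The documents do not say that costs enter unscaled. Scaling or interpolating is commonly left to an economic analysis plan, and at a constant rate tripling the T1 figure recovers the whole cost. EQ-5D-5L is also collected only at the assessment points, so the QALY side is interpolated too. Programme costs are counted apart from recall, and the cost questionnaire still to be developed might fill the gap. All this stands, and it rules out any dollar figure for the bias. What remains is that the scheduled survey does not observe weeks 1-8, and that the observed weeks are a doubtful basis for extrapolating to them.

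**On the missing contrast.** A reader might infer that support could be declared good value while self-help is the better buy. That does not follow, because supported against self-help is the first planned comparison and tests just that. It is also fair that the data are collected and the point estimates can be recovered by subtraction. But the plan does not promise the estimate, and subtraction gives no interval.

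**On the criterion.** A reader might infer that the rule would declare a dominated arm cost-effective. The wording refers to a QALY gained, which presupposes a gain, and nothing says that a negative ratio would be read as success. How often such a misreading could occur depends on inputs the documents do not give. Only a point of wording is left.

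**Conclusion.** The point holds in this limited form. Half of Aim 3, pure self-help against WLC, has no planned ICER. This is a contradiction within the article; it lies in the stated analysis and not in the data. External service use is observed for one third of each economic horizon (28 of 84 days, 56 of 168 days), in a window that contains the nominal end of the programme and the offer of BEeT to WLC participants. The coverage figures assume that all arms are surveyed at weeks 12 and 24 and that the survey in Table 2 is the only resource-use instrument. The effect on the ICER is unknown in size and direction. The wording of the $50,000 criterion is a minor matter. The primary clinical outcome is untouched; a stated aim and the main economic hypothesis are affected.

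**What to change.** 1. Add pure self-help against WLC to the economic analysis and report a fully incremental three-arm comparison: order the arms by cost, remove dominated options, and give ICERs between those that remain. This needs no new data. Since WLC participants are offered BEeT after ten weeks, the contrast approximates self-help against no treatment only at the 12-week horizon; later it is immediate against delayed access.
2. Add the 28-day service-use question to the existing online check-ins at weeks 4 and 8 for participants not yet past them. With T1 this observes 28 + 28 + 28 = 84 of 84 days. The cost is a slightly longer questionnaire at two existing contacts. Because the study began in May 2020, it also means mixed data across earlier and later participants.
3. For participants already past those weeks, and for weeks 13-20 in everyone (168 − 84 − 28 = 56 days), state the extrapolation used and vary it in the planned sensitivity analysis.
4. Reconcile the ten-week and 12-week statements of T1 for WLC, so that the recall windows are known to match across arms.
5. Write the criterion as incremental net monetary benefit above zero at $50,000 per QALY, so that its meaning does not depend on the sign of the QALY difference. This changes wording only.

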#### Implementation questionnaire

Self-designed questionnaires will be used to assess treatment implementation from the perspective of participants, clinicians delivering supported BEeT, and trial site managers. The outcome variables include acceptability, adoption, appropriateness, feasibility, fidelity, and sustainability [68]. Feedback will be sought from participants regarding their experience of using the BEeT intervention and clinicians will be asked about their perception of the suitability of the supported BEeT program for patients in their service. Site managers will be asked questions to assess their willingness to embed a supported self-help program, such as BEeT, within their clinical service. Question responses include a combination of 5-point Likert scale and checkbox answers.

#### Compliance

Measures of compliance will be monitored via the online platform on which the BEeT intervention is hosted. These include the number of self-monitoring entries logged per day, the amount of time taken to complete each online BEeT session, and the time between completion of each BEeT session. The compliance data will be included in statistical analyses of intervention response to determine their effects on key clinical and health economic outcomes.

## Participant timeline

See Fig. 1 for the individual participant timeline.

### Sample size

The power calculation is based on EDE-Q outcome data from a recent pilot study of BEeT [49]. The pre- to post-treatment change in objective binge episode frequency, rather than the frequency of purging was chosen as the basis for the power analysis given that not all of the participants in the current study will have engaged in purging behaviours. Accounting for multiple comparisons in the testing procedure, an alpha of 0.05 was adjusted to 0.017 under the Bonferroni method. Using a minimum of 14.9 and maximum of 23.7 for the group means (based on the findings of Barakat et al. [49]), and assuming an adjusted significance level of 0.017, a power of 0.8, and an effect size Cohen’s f = 0.3, a sample size of 48 participants is required in each of the three conditions. By applying a dropout rate of 16% (based upon findings of Barakat et al. [49]), 55 participants are needed in each group. Due to potential resourcing and time limitations, consideration was given to a worst-case scenario of sample size to be recruited. Given this, simulations of the possible impact of reduced sample size was analysed varying the parameters of an effect size (0.25–0.34) and alpha (0.01–0.025). Our worst case scenario indicates that with an effect size of 0.2, alpha of 0.017, and a sample size of 99 participants recruited, the study will have a power of 0.6. This sample size is supported by previous RCTs on eTherapies for eating disorders which have yielded very similar values in their power analyses [69–71]. The power analysis was calculated using STATA (Version 15) [72].

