Several systematic reviews have concluded that digital self-help interventions are effective in reducing eating disorder behaviours [33–40]. There is evidence to also suggest that the treatment outcomes of self-help interventions are significantly enhanced by the addition of low-intensity support from a clinician, such as a fortnightly, check-in email or phone call [12, 39, 41–43]. Supported self-help interventions only demand one-fifth of the therapist contact hours required for a complete CBT course, meaning they can be delivered in settings with low resources and capacity limits [42]. The provision of clinician support as an adjunct to self-help programs has been suggested as a viable solution to one of the most powerful critiques of digital interventions, that being the high rates of non-adherence [37, 38]. Internet-delivered CBT has the highest dropout rates of all ED treatments, ranging up to 47.2% [44]. Given the potential impact of non-adherence upon the therapeutic outcomes for patients, several reviews have highlighted the need for ongoing development and examination of novel digital treatments, with the aim of reducing the discrepancy in adherence between online platforms and more traditional modes of face-to-face treatment delivery [35, 37, 38].

Two large published studies provide evidence for the use of online CBT-based, self-help programs for individuals with BN. As part of a randomised controlled trial (RCT) conducted by Sánchez-Ortiz et al. [45] significant improvements were reported in a sample of 75 patients with full or subthreshold BN following completion of an eight-session online CBT-based program. Abstinence rates were comparable to those of patients receiving a manual-based CBT self-help intervention and face-to-face CBT program [46, 47]. Similarly, Pretorius et al. [48] observed significant reductions in BN symptomology in response to an online CBT program, supplemented with email support from a clinician and peer support via message boards, which were maintained at six-month follow up. An abridged version of BEeT has also been successfully piloted proving its acceptability, feasibility, and effectiveness in reducing core symptoms of BN [49].

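### The dropout inflation is wrong: keeping 48 per group after 16% loss needs 58 recruited, not 55, although the cost in power is only about 2 points

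*Protocol article*

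**What the plan says.** The Sample size section of the protocol article builds the recruitment figure in two steps.

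- **Base size.** For multiple comparisons, "an alpha of 0.05 was adjusted to 0.017 under the Bonferroni method". The calculation then proceeds by "assuming an adjusted significance level of 0.017, a power of 0.8" and an effect size given as Cohen's "f = 0.3, a sample size of 48 participants is required in each of the three conditions". The number of groups is confirmed under Trial design and setting: "This study is a multisite, three-arm randomized controlled trial inclusive of two active interventions and a WLC".
- **Allowance for dropout.** "By applying a dropout rate of 16% (based upon findings of Barakat et al. [49]), 55 participants are needed in each group".

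The section gives no total for this target; three groups of 55 make 165.

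**The concern.** The 48 per group is presented as the number required for power 0.8. The purpose of inflating for dropout is that this number is still there after the stated loss. Taking 16% away from 55 leaves fewer than 48, so the two consecutive statements do not agree. At stake is the figure a reader will take as the recruitment target, and the claim that this target delivers power 0.8 at the dropout the authors themselves assume.

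**Working it through.** **Inputs**, all from the Sample size section: three equal groups, f = 0.3, alpha = 0.017, power 0.8, dropout 16%, base size 48 per group, recruited size 55 per group. The section also gives the range of group means ("Using a minimum of 14.9 and maximum of 23.7 for the group means"), but this is not needed once f is fixed. The test is not named. I take it to be the one-way omnibus F test, because the effect size is given as Cohen's f and because this test returns the stated 48.

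**Step 1: reproduce the 48.** Power is the probability that a noncentral F variable with 2 and N − 3 degrees of freedom and noncentrality N × f² exceeds the central F critical value at alpha.

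- 47 per group: N = 141, noncentrality 141 × 0.09 = 12.69, power 0.793.
- 48 per group: N = 144, noncentrality 144 × 0.09 = 12.96, power 0.803.

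The smallest size reaching 0.8 is therefore 48, as stated. With the unrounded alpha of 0.05/3 the power at 48 is 0.801, so the answer is the same. There is no slack in the 48 to absorb a shortfall.

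**Step 2: the dropout step.** To keep n after a proportion d is lost, recruit n/(1 − d).

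- 48/(1 − 0.16) = 48/0.84 = 57.14, so 58 per group, or 174 in total.
- Check: 58 × 0.84 = 48.7, while 57 × 0.84 = 47.9, just under 48.
- Stated figure: 55 × 0.84 = 46.2 per group, or 165 × 0.84 = 138.6 in total.
- Dropout that 55 does cover: 1 − 48/55 = 12.7%.

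**Step 3: where 55 may come from.** Multiplying in place of dividing gives 48 × 1.16 = 55.68. That rounds up to 56 and becomes 55 only if the fraction is dropped. This is my inference; the section does not show the formula.

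**Step 4: power with 55 recruited and 16% lost.**

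| Analysed per group | Power (f = 0.3, alpha 0.017) |
|---|---|
| 46 | 0.782 |
| 46.2 | 0.784 |
| 48 | 0.803 |

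Averaging over binomial dropout from 165 gives 0.783. The shortfall in recruitment is 58 − 55 = 3 per group, or 9 in total (9/174, about 5%).

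**The case against.** **The effect is lost in rounding.** The section gives power to one decimal, and 0.78 rounds to 0.8. The loss is about 2 points. This stands as an argument about weight. It does not rescue the 55, which is a count and differs from 58 by more than rounding.

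**The planned analysis does not discard dropouts.** The Statistical methods section specifies intention to treat, multiple imputation and a mixed model with age, illness severity and length of illness as covariates. This also stands in part. The 0.78 assumes that people who drop out contribute nothing and that nothing is adjusted for. If all 165 contributed fully, the same F test would have power 0.865. How much of that gap would be recovered cannot be worked out, because the article gives no correlations between covariates and outcome and no description of the missing data. But a calculation that inflates for dropout treats dropouts as lost, and on that basis 55 is too few.

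**The target is not binding.** The same section openly considers recruiting only 99. Against that, 9 participants is a small difference. The fallback is a separate scenario, though, and does not make the main figure correct.

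**A stronger reading that the article does not support.** A reader might infer that 16% is itself far too low. The Introduction says "Internet-delivered CBT has the highest dropout rates of all ED treatments, ranging up to 47.2"%, and describes the source of the 16% in the words "An abridged version of BEeT has also been successfully piloted". Neither passage carries that conclusion. The 47.2% is an upper extreme across internet-delivered programmes, and the Introduction raises it when discussing non-adherence, not missing primary-outcome data. The Discontinuation criteria section removes disengaged participants, but does not say that their post-intervention questionnaire is no longer sought. A pilot of the same programme is a normal source for a dropout assumption, and nothing in the article shows that the full version would lose more people.

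**Conclusion.** The point holds, and it is minor. On the article's own inputs the recruitment figure should be 58 per group (174 in total), not 55 (165 in total), if 48 are to remain after 16% dropout. As written, about 46 per group remain and power is about 0.78. That figure rests on four assumptions: the one-way omnibus F test, f = 0.3 with alpha 0.017, complete cases only, and no covariate adjustment. Imputation and covariates could bring some power back.

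It would be wrong to conclude from this that the trial is materially underpowered. The error is in one stated number, and its consequence at the stated dropout is about 2 power points.

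**What to change.** Change one sentence in the Sample size section, in one of two ways.

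- **Keep 55 per group** and state that 16% dropout leaves about 46 per group, with complete-case power of about 0.78 at f = 0.3 and alpha 0.017. No additional participants are needed; the stated power becomes slightly less favourable.
- **Correct the figure to 58 per group** (174 in total) if power 0.8 after 16% dropout is to be claimed. This adds 3 participants per group, 9 in all.

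As the Trial design and setting section says that the study commenced in May 2020, the first is the easier correction. Tabulating power at further dropout rates would be a matter of preference and is not needed to put this right.

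### The worst-case power of 0.6 does not follow from its inputs: effect size 0.2, alpha 0.017 and 99 participants give about 0.25

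*Protocol article*

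**What the plan says.** All of this is in the Sample size section of the protocol article.

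- **Significance level:** "an alpha of 0.05 was adjusted to 0.017 under the Bonferroni method".
- **Base case:** "assuming an adjusted significance level of 0.017, a power of 0.8", and Cohen's "f = 0.3, a sample size of 48 participants is required in each of the three conditions". Dropout of 16% then raises the target to 55 per group.
- **Reduced samples:** because resources and time might fall short, smaller samples were examined by simulation, "varying the parameters of an effect size (0.25–0.34) and alpha (0.01–0.025").
- **Worst case:** with "an effect size of 0.2, alpha of 0.017, and a sample size of 99 participants recruited, the study will have a power of 0.6".

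The section describes no separate model or test for the worst case.

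**The concern.** The worst case combines a smaller effect than the base case (0.2 against 0.3) with a smaller sample (99 against 144 analysed), at the same alpha. Power falls only from 0.8 to 0.6. That is too small a loss: the noncentrality parameter N × f² drops from 144 × 0.09 = 12.96 to 99 × 0.04 = 3.96, less than a third. The effect size of 0.2 is also not among those the paragraph says were examined.

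This is the article's only statement of what the trial could detect if recruitment falls short. The Discussion reports that COVID-19 delayed recruitment significantly, so a reduced sample is a real prospect. A reader weighing whether 99 is acceptable is told that such a trial keeps 60% power for an effect smaller than planned. If the true figure is about 25%, roughly three in four such trials would miss that effect.

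**Working it through.** **Inputs.** From the Sample size section: alpha 0.017; base-case f = 0.3, power 0.8, 48 per arm; dropout 16%; worst case 0.2, 99 recruited, power 0.6. From Trial design and setting: three arms. Equal allocation is assumed from the equal group sizes (99 = 33 per arm). The worst-case effect is read as Cohen's f, the scale of the base case.

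**Method.** One-way F test with three equal groups:

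Power = P[F′(2, N − 3; λ) > F crit], with λ = N × f² and F crit the upper 0.017 point of F(2, N − 3).

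**Step 1: reproduce the base case.** N = 3 × 48 = 144 and f = 0.3, so λ = 144 × 0.09 = 12.96. F crit (2, 141) = 4.195 and power = **0.803**. With 47 per arm (N = 141), power is 0.793. So 48 per arm is the smallest size that reaches 0.8, exactly as stated, and the method matches the article's.

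**Step 2: worst case as stated.** N = 99 and f = 0.2, so λ = 99 × 0.04 = 3.96. F crit (2, 96) = 4.252 and power = **0.245**, against 0.6 stated. The ratio is 0.6 / 0.245 ≈ 2.4.

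**Step 3: where 0.6 arises.** N = 99 and f = 0.3 give λ = 8.91 and power = **0.596**. Exactly 0.6 needs f = 0.301.

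**Step 4: power by effect size, alpha 0.017.** The 83 is 99 × 0.84 = 83.2.

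| f | N = 99 | N = 83 |
|---|---|---|
| 0.20 | 0.245 | 0.197 |
| 0.25 | 0.411 | 0.333 |
| 0.30 | 0.596 | 0.498 |
| 0.34 | 0.733 | 0.632 |

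**Step 5: check against the full trial.** At f = 0.2, the planned 144 analysed give 0.385, and all 165 (3 × 55) without dropout give 0.449. A trial of 99 cannot have 0.6 for an effect at which the full trial stays below 0.45.

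**Step 6: what would be needed.** At f = 0.2 and alpha 0.017, power 0.6 needs N = 219 (73 per arm) and power 0.8 needs N = 318 (106 per arm). At N = 99, power 0.8 needs f = 0.36; at N = 83, f = 0.40.

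**Step 7: other readings of the worst case.**

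| Reading | Power |
|---|---|
| f = 0.2, N = 99, alpha 0.025 | 0.294 |
| f = 0.2, N = 99, alpha 0.05 | 0.401 |
| f = 0.2, 99 per arm (N = 297), alpha 0.017 | 0.768 |
| f² = 0.2, N = 99, alpha 0.017 | 0.950 |
| eta² = 0.2 (f = 0.5), N = 99, alpha 0.017 | 0.984 |
| Pairwise t test, 33 per arm, d = 0.4, alpha 0.017 | 0.21 two-sided, 0.30 one-sided |
| Pairwise t test, 33 per arm, d = 0.2, alpha 0.017 | 0.06 two-sided, 0.09 one-sided |

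None gives 0.6.

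**The case against.** The strongest reply is that the power may be right and the effect size misprinted, 0.2 for 0.3. The match at f = 0.30 and the out-of-range 0.2 both point that way, and the section speaks of a worst case for sample size, which allows an unchanged effect. This stands as a possible cause, but the documents do not settle it. It leaves the sentence wrong as printed, since a reader still attaches 0.6 to an effect of 0.2.

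A second reply is that the reduced-sample figures came from simulations whose model is not shown, and that the planned analysis adjusts for baseline severity. An analysis of covariance with a baseline correlation of about 0.75 does give 0.605 at f = 0.2 and N = 99. But no such correlation is stated, and the same adjustment would put the base case at 0.996 with 48 per arm instead of 0.8. Repeated-measures calculations can also span 0.6 under unstated correlations, but they give 0.87 or more for the base case.

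Third, the figures at 83 treat dropouts as contributing nothing, whereas Statistical methods plans intention to treat with multiple imputation. That is fair: they are approximations. Imputation does not restore all the lost information, however, so 0.245 remains the favourable value.

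Fourth, the article sets no rule to stop at 99, and its main calculation reproduces. Both points are correct. They limit the consequence but do not make the figure right.

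**Conclusion.** The concern holds. Effect size 0.2, alpha 0.017, 99 participants and power 0.6 cannot all be true under the test that yields the article's own 48 per arm. As stated, power is about 0.25, some 35 percentage points lower, and about 0.20 if 16% are lost. The result assumes three equal arms and an effect size on Cohen's f scale; reading 0.2 as a pairwise standardised difference gives still lower power. That 0.6 came from f = 0.30 is an inference from the numerical match. The error does not depend on it: if 0.3 was meant, the effect size is wrong, and if 0.2 was meant, the power is wrong. In the first case, 0.6 still holds only if nobody drops out; with about 83 analysed it falls to about 0.50.

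**What to change.** Replace the worst-case sentence with figures that reproduce. For example: with 99 participants analysed and alpha 0.017, power is 0.60 for f = 0.30, 0.41 for f = 0.25 and 0.25 for f = 0.20; if 16% drop out (about 83 analysed), it is approximately 0.50, 0.33 and 0.20. Label the effect size as Cohen's f and mark the dropout figures as complete-case approximations. Add that at this size the trial has 80% power only for f of about 0.36 (99 analysed) to 0.40 (83 analysed), above the planned 0.3, so a non-significant result would be inconclusive for the planned effect. Make the stated range of simulated effect sizes agree with the values reported.

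These figures are correct whichever number was misprinted. The cost is a short rewrite and a less favourable figure; no participants are added and the design does not change.
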